**Inclusion criteria**
Enrolled participant of the Oxford BioBankHealthy adults aged 40 years and olderAble to ambulate (with or without a walking aid)Willing to wear multiple sensors over 3 days and 4 nights of data collection
**Exclusion criteria**
Unable to speak or understand EnglishSelf-reported neurological conditions or diagnosed sleep impairmentSelf-reported clinicians, teachers, caregivers, or anyone working in environments where image capture would be inappropriate and who cannot commit to 3 consecutive days of image capture outside of these sensitive environmentsUnwilling to wear all the monitors according to the study protocol

### Study Timeline

A study timeline is presented in Figure 1, outlining the overall data collection period. Data collection will be conducted in the free-living environment for 3 full days and 4 consecutive nights. Following receipt of consent, an in-person study setup visit is arranged, wherein 2 members of the research team will meet the participant at their home to set up and deploy the wearable sensors, camera, and under-mattress sleep analyzer for the data monitoring period, in addition to the PSG sleep assessment for the first night only. One night of PSG was chosen to balance participant and researcher burden with the inclusion of a gold standard sleep assessment. The distribution of ambulatory wearable sensors across the body is presented in Figure 2, with further description in the following methodological subsections.

**Figure 1. F1:**
[figure not shown]
Overview flowchart of study activities during the data collection window. Green activities are conducted by the OxWEARS research team, and blue activities are conducted or collected by the study participant. ECG: electrocardiography; PSG: polysomnography.

**Figure 2. F2:**
[figure not shown]
Distribution of wearable sensors for 3-day and 4-night ambulatory monitoring, including wrist, waist, thigh, and ankle accelerometers; a chest-mounted ECG and accelerometer patch; and an automated camera. *Denotes ground-truth or reference measurements (image designed by Freepik).

### Ground-Truth ECG Data Collection

Ground-truth cardiac monitoring will be conducted using a clinical-grade single-lead wearable ECG patch (Bittium Faros 180; Bittium) affixed in a vertical orientation directly to the skin on the chest immediately inferior to the jugular notch and superficial to the sternum. Before adhesion, participants with chest hair will be instructed to shave the designated area to ensure adequate adhesion as per manufacturer guidelines. Continuous single-lead ECG data will be collected at 250 Hz and logged directly onto the ECG device for the entirety of the monitoring period (24 hours/day). In addition to raw ECG data, the monitor will be set to record continuous raw triaxial accelerometer data at the chest at a sampling rate of 100 Hz and with a dynamic range of ±4*g*.

### Ground-Truth Physical Behavior Data Collection

To obtain ground-truth data on everyday activities, participants will wear a first-person perspective video camera (MIUFLY) during waking hours for 3 days, mirroring procedures from prior studies using first-person image capture to annotate physical activity and sedentary behavior [7,21]. In this study, a wearable camera is worn by the participant via a chest harness, neck mount, clip, or lapel and continuously records video during participant waking hours. Previous automated camera studies of this nature have reported wear time compliance of more than 80% [22,23]. No audio is captured by the camera, and all footage is encrypted on the device so that only the research team can download and view the video. Participants will be instructed on how to cover the camera or pause data collection at any time when they desire privacy or feel uncomfortable or unsafe. Examples of this include using the bathroom (public or private), public changing rooms, interacting with unrelated children, or working in contexts where intellectual property must be protected.

### Ground-Truth Sleep Assessment

On the first study night, ground-truth sleep data will be collected with an ambulatory diagnostic multichannel PSG system (SOMNO HD Eco; S-Med Limited). The electroencephalogram (EEG) array will be attached in accordance with the 10-20 system of electrode placement [24]. The montage and recording settings (30-second epochs, 256 Hz sampling rate for EEG channels) will conform to the American Academy of Sleep Medicine (AASM) recommendations [25]. The following channels will be recorded: scalp EEG (F3, F4, C3, C4, O1, and O2), bilateral references on the mastoid processes (M1 and M2), grounding electrode (placed on FpZ), a common scalp reference electrode (Cz), bilateral electro-oculogram, 2-lead ECG, and 3-lead submental electromyography. Participants will be asked to change into sleeping clothes prior to sensor setup to minimize the risk of electrode disturbance. Prior to recording, researchers will check signal quality via a tablet and replace electrodes with high impedance values (>5 kΩ). The in-home sleep study will be conducted for 1 night only. Participants will be instructed to blink several times to indicate lights off at the time of their choosing. Participants will be instructed on how to remove the electrodes themselves following sleep, and a member of the research team will make a return visit the morning following the at-home visit to collect the PSG equipment and answer any further questions regarding the study.

### Wearable-Based Physical Behavior Monitoring

Participants will be asked to wear 5 stand-alone wearable devices continuously (24 hours/day) throughout the course of the study period (Figure 2). The wear locations for the sensors were selected based on their popularity in previous validation studies [4,5]. The recording specifications of each device and sensor are detailed in Table 1. Wrist-measured physical behavior data will be collected using a combination of research-grade and consumer-grade devices. Specifically, a multimodal research-grade device (ActiGraph LEAP: ActiGraph LLC) consisting of triaxial accelerometer, gyroscope, and PPG sensors will be worn on the participant’s dominant wrist. Similarly, a consumer-grade device (Fitbit Sense 2; Fitbit by Google) with comparable multimodal sensors to the ActiGraph LEAP will be worn on the participant’s nondominant wrist, according to manufacturer’s instructions.

**Table 1. T1:** Wearable device data capture.

Device	Location	Sensors and recording settings	Heart rate
Bittium Faros 180	Chest	Accelerometer: 100 Hz, ±4*g*	1-channel ECG^a^: 250 Hz
ActiGraph LEAP	Dominant wrist	Accelerometer: 32 Hz, ±8*g*; gyroscope: 128 Hz and ±2000 dps^b^	PPG^c^: green (530 nm), 128 Hz
Fitbit Sense 2	Nondominant wrist	60 s epoch proprietary phenotypes	60 s epoch heart rate average
ActiGraph GT3X-BT	Waist or hip	Accelerometer: 100 Hz, ±8*g*	^d^—
Axivity AX6	Dominant thigh	Accelerometer: 100 Hz, ±8*g*; gyroscope: 100 Hz, ±2000 dps	—
Axivity AX6	Dominant ankle	Accelerometer: 100 Hz, ±8*g*; gyroscope: 100 Hz, ±2000 dps	—

a ECG: electrocardiogram.

b dps: degree per second.

c PPG: photoplethysmography.

d Not applicable.

Participants will wear an ActiGraph GT3X-BT monitor (ActiGraph LLC) on their hip continuously throughout the data collection period, removing it only for water-based activities. The device will be worn using an adjustable belt strap, with a buckle for easier removal.

For thigh monitoring, a medical-grade hypoallergenic adhesive dressing will be used to affix an accelerometer (Axivity AX6; Axivity Ltd) on the anterior aspect of the participant’s dominant thigh, wrapped in a nitrile sleeve for protection. The Axivity AX6 houses a triaxial accelerometer and triaxial gyroscope, which will both record at a sampling frequency of 100 Hz and dynamic sensor ranges of ±8*g* and ±2000 degrees per second, respectively.

As an additional measurement point for physical activity, a further Axivity AX6 device (with matching recording characteristics) will be mounted on the dominant-side ankle, wrapped in a nitrile sleeve using medical adhesive tape. This is of specific interest for potential step count validation [26], for which a separate study including video-captured daily steps with concurrent ankle- and wrist-worn Axivity AX6 devices will be conducted to assess the validity of the ankle as a suitable ground-truth measure for step count in 50 adults, incorporating machine learning methods to estimate step count compared with proprietary algorithms assessed previously [26]. This model will then be applied to OxWEARS to compare step count from the ankle with each of the other wear locations (chest, both wrists, hip, and thigh).

### Nearable-Based Sleep Assessment (Under-Mattress Sensor)

In addition to the ground-truth PSG sleep assessment, a popular consumer-grade sleep device (Withings Sleep Analyzer; Withings) will be set up by the researcher for the full 4 nights of the study. The Withings Sleep Analyzer will be placed under the participant’s mattress in line with where the heart would be while the participant lies in bed. It uses ballistocardiography and a built-in microphone to estimate sleep duration, efficiency, sleep onset latency, sleep staging (awake, light, deep, or rapid eye movement sleep), as well as breathing rate and snoring events, using proprietary algorithms. It has shown some early promise as a potential “nearable” device for individuals to monitor long-term sleeping patterns without the need to physically wear a device [27].

### Subjective Sleep Assessment

As a final complementary measure of sleep duration and quality, participants will additionally be asked to complete a standardized self-report sleep diary on each of the 4 study nights [28], which captures times the participant got into bed, went to sleep, woke up, and got out of bed. We have further adapted this to capture information on perceived sleep quality and whether any naps were taken outside of the primary sleep window (Multimedia Appendix 3).

### Data Processing and Analysis

Physiological reference metrics derived from the ground-truth clinical-grade cardiac monitor will include participant heart rate and heart rate variability. There is ongoing work to develop and validate an ECG algorithm, which will be made publicly available in the future. During this process, clinical experts with extensive experience will review ECGs for RR intervals to determine algorithm performance. Derived heart rate and variability will be calculated on a per-epoch basis in 10-second windows and will serve as the ground-truth labels of heart rate for the study. Comparisons will then be made between these cardiac monitor–derived metrics and PPG-derived metrics [29] from both wrist-worn devices in terms of epoch-level accuracy and agreement across participant age, sex, and BMI subgroups.

Physical activity behaviors derived from the camera will take the form of video annotation of labeled activities based on posture (eg, lying, sitting, and standing) and whole-body movements (eg, walking, running, and cycling), in line with previous research [30]. Each participant’s camera data will be annotated by an annotator who has completed a rigorous training regimen and is certified for annotation after consistently reaching a κ agreement of >0.8 against a series of day-long reference participants. If multiple annotators are required, we will additionally assess for interrater reliability scores. Further annotation and assessment will be conducted against machine learning–based automated image and video annotations [31]. These annotations will serve as the basis for retraining machine learning behavior classification models to better identify periods of sedentary, light, moderate, and vigorous physical activity [9,32].

Ground-truth sleep metrics, including time of sleep onset, waking time, and sleep staging, will be scored according to the AASM 2023 guidelines [25] by a single AASM-accredited sleep scientist with additional European Sleep Research Society accreditation and more than 15 years of experience working with EEG data. Sleep stages (non–rapid eye movement sleep [stages N1, N2, and N3], rapid eye movement, and awake) will be assigned for every epoch (30 seconds). A subsample of recordings (10%‐20%) will be scored by a secondary accredited researcher to assess interrater reliability. As per recommendations in the field, scoring will be adjusted until interrater agreement reaches >80%. Similar to the physical activity behavioral ground-truth annotations, sleep annotations derived from the in-home PSG will serve as the basis for comparison of sleep time, sleep efficiency, and sleep staging derived from other accelerometers and the under-mattress sleep nearable, in addition to current accelerometer-based machine learning sleep models [33,34].

Data quality will be assessed regularly throughout the data collection period to check protocol adherence. This will involve processing the raw accelerometer data from the research-grade wearables through existing analytic software, such as Biobank AccelerometerAnalysis (University of Oxford) [8] and Stepcount (University of Oxford) [35], to assess device recording duration and nonwear detection based on accelerometer thresholds. The Fitbit- and Withings-derived data will be checked at the summary level to flag possible poor compliance. PSG data quality will be assessed within the manufacturers' software using an automated sleep-stage classification system. We will report on the technical validation of the data when we publish the complete dataset, including the number of participants and the volume of camera-labeled data, both separately and when combined with concurrent data from other devices.

The primary aim of this study is to collect a high-quality validation dataset to facilitate new ways of analyzing time-series wearable data. As such, there will be many future imaginative analyses of these data that we do not anticipate at present. At present, we anticipate that mean precision, recall, *F*_1_-score, Cohen κ, and accuracy will be used to evaluate model performance for all comparisons with ground-truth labels. Additionally, summary metrics will be assessed against the ground-truth measure using mean absolute bias, mean amplitude percentage error, Cohen κ [36], and Bland-Altman plots [37].

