### Recruitment

OxWEARS is a cross-sectional study and will recruit a target sample of 160 participants from the Oxford BioBank [19]. A sample size of 160 will provide 80% power to detect a difference of 0.05 in Cohen κ score (effect size=0.25, assuming an SD of 0.25 from previous studies [20]) between 3 age groups using a fixed effects one-way ANOVA test (α=.05). The Oxford BioBank is a population-based cohort of approximately 9000 participants aged 25 to 55 years recruited in Oxfordshire, United Kingdom, from 1999 onward. Inclusion and exclusion criteria for this study are presented in Textbox 1. Recruitment will target the creation of a final study cohort evenly balanced by sex, age (40‐54 years, 55‐64 years, and ≥65 years), and BMI (18.5‐25 kg/m^2^, 25‐30 kg/m^2^, and >30 kg/m^2^). The distribution of invitations will be regularly rebalanced to achieve 13 to 14 participants in each subgroup by the end of the study.

Textbox 1.Inclusion and exclusion criteria.

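### The double-scored PSG nights both measure interrater reliability and decide when score adjustment stops, so agreement computed after adjustment cannot estimate reliability

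*Protocol article*

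**What the plan says.** All statements on scoring are in the protocol article under Data Processing and Analysis.

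- **Scorer.** The reference sleep metrics are scored "by a single AASM-accredited sleep scientist with additional European Sleep Research Society accreditation".
- **Unit.** Five classes (N1, N2, N3, REM, awake) "will be assigned for every epoch (30 seconds").
- **Second scoring.** A subsample of 10%-20% "will be scored by a secondary accredited researcher to assess interrater reliability".
- **Rule.** In the next sentence, with an appeal to recommendations in the field, "scoring will be adjusted until interrater agreement reaches >80" percent.
- **Use.** The "sleep annotations derived from the in-home PSG will serve as the basis for comparison of sleep time, sleep efficiency, and sleep staging" from the accelerometers and the under-mattress sensor.

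The number of recordings comes from two other sections. Under Recruitment the study "will recruit a target sample of 160 participants from the Oxford BioBank", and under Ground-Truth Sleep Assessment, "The in-home sleep study will be conducted for 1 night only".

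**The concern.** The two sentences on double scoring give one exercise two jobs that do not fit together. The first treats agreement between scorers as a result to be found. The second treats it as a target, with the scores changed until it is met. A figure taken after that process shows that the process ended. It does not show how well two accredited scorers agree on these recordings.

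This matters because one person labels every night, so the double-scored subset is the only human check on reference error that the article describes. Error in the reference limits the κ, *F*₁-score and accuracy that any device can show against it. If the published reliability has been brought up to a threshold, users of the open dataset cannot separate device error from scorer error. The article calls a high-quality validation dataset its primary aim, so the quality of the reference is central.

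A second question follows from the first. Scorer disagreement can be seen only in the double-scored nights. If the adjustment stays there, the released labels come from two different procedures.

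**Working it through.** The article gives no sample size, expected value or precision for interrater agreement, so there is no stated figure to reproduce. The check follows the rule through.

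**Inputs from the article.** Target of 160 participants, one PSG night each, double-scored share s = 0.10 to 0.20, threshold 0.80.

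**Assumed input.** First-pass agreement a₀ before any adjustment. The article gives none, so a range is shown.

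**Step 1: how many nights are double-scored?**
- 160 × 0.10 = 16 and 160 × 0.20 = 32 double-scored.
- 160 − 16 = 144 and 160 − 32 = 128 single-scored, which is 90% and 80% of recordings.

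**Step 2: what does the rule do to the agreement figure?** Taking the threshold as the floor, post-adjustment agreement is at least max(a₀, 0.80).

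| a₀ (assumed) | After adjustment, at least | Shortfall hidden |
|---|---|---|
| 0.70 | 0.80 | 10 points |
| 0.75 | 0.80 | 5 points |
| 0.78 | 0.80 | 2 points |
| 0.82 | 0.82 | none; rule not triggered |
| 0.85 | 0.85 | none; rule not triggered |

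Below the threshold, different starting values give the same floor, so the final figure cannot show a failure. Above it, the figure is what the two scorers actually found.

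**Step 3: what if only the double-scored nights are adjusted?** Assume also that the single-scored nights would have shown the same a₀ had they been double-scored. Agreement over the whole set is then s × 0.80 + (1 − s) × a₀.

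| a₀ (assumed) | s = 0.10 | s = 0.20 |
|---|---|---|
| 0.70 | 0.080 + 0.630 = 0.710 | 0.160 + 0.560 = 0.720 |
| 0.75 | 0.080 + 0.675 = 0.755 | 0.160 + 0.600 = 0.760 |
| 0.78 | 0.080 + 0.702 = 0.782 | 0.160 + 0.624 = 0.784 |

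Each value is below the 0.80 that the subset would show.

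**Step 4: what if adjustment means recalibration and rescoring of every night?** The labels are then consistent across the dataset and Step 3 falls away. Step 2 stays for any agreement computed again on the same 16-32 nights, because those nights were used to reach the target.

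**The case against.** The strongest reply is that the text is brief rather than wrong. It does not say that the adjusted figure is the one to be published, and nothing rules out reporting first-pass agreement. Adjustment may mean that the scorers align their use of the scoring rules and the first scorer then applies them throughout. An article can leave that procedure to a fuller document, and this one promises a technical validation report with the dataset. The first scorer is accredited and has more than 15 years of EEG experience, so first-pass agreement may exceed 80% and the rule may never operate.

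Much of this stands, and it rules out three stronger readings that a reader might infer:

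- *The reported reliability is guaranteed to exceed 80%.* This follows only if the post-adjustment figure is the one reported, which the article does not say.
- *Only the double-scored labels change.* The article does not limit adjustment to the subset.
- *The bar is raw percent agreement, and so weaker than the camera standard.* The article does not name the statistic. Converting 80% raw agreement to κ would need a stage distribution that it does not give. The camera annotators are "certified for annotation after consistently reaching a κ agreement of >0.8" during training, before they annotate. That threshold serves another purpose, so a different one for PSG is no contradiction.

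The reply does not remove the core point. Adjusting until a threshold is passed is a rule the article states, and it directly follows the sentence that gives the second scoring its purpose. Consensus work can improve labels, and field practice may support it for that. The same nights cannot then also supply an independent reliability estimate.

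**Conclusion.** The point holds in conditional form and should be corrected. Without any assumption, agreement computed after adjustment on the double-scored nights exceeds 80% by construction and is not an estimate of scorer reliability.

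The size depends on what the article leaves open. If first-pass agreement exceeds 80%, there is no effect. If it were 70%-78% (assumed) and the adjusted figure were reported, the report would hide a shortfall of 2-10 percentage points. If adjustment were also confined to the subset, 128-144 of the 160 nights would keep unadjusted labels and the reference standard would differ between subsets. The counts assume that the target of 160 is met with one usable recording each.

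**What to change.** Replace the adjustment sentence with a rule that separates measurement from correction:

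1. The second scorer scores the 10%-20% subsample blind to the first scorer's labels.
2. First-pass agreement, before any discussion or change, is the reliability result. It is given as percent and κ, overall and by sleep stage.
3. Discordant epochs are used only to clarify scoring rules. Any change of rule is applied to all recordings, including the 128-144 single-scored nights.
4. Post-adjustment agreement on the same recordings is not presented as reliability. If agreement after a rule change is wanted, it is measured on freshly double-scored nights and shown beside the first-pass figure.

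Items 1, 2 and 4 need a change of wording and retention of the first-pass score files, with no additional scorer. The optional re-estimate in item 4 would take more second-scorer time. There are two downsides: the reported agreement may fall below 80%, and the first scorer may have to re-check recordings if a rule changes. With 15 of 160 participants enrolled by May 2025, settling this early keeps any re-checking small.

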### Metadata Description

Our complete dataset and metadata will be hosted by the Oxford University Research Archive under the Creative Commons “Attribution 4.0 International (CC BY 4.0)” license. Raw accelerometry, ECG, and PPG data will be provided as compressed CSV files in folders for each participant. We will provide separate CSV files containing a dictionary of annotation labels for scored PSG data, a full annotation schema, labels for wearable camera data, and participant characteristics (age category, sex, and BMI category).

